### Study procedures for prospective cross-sectional analysis

2.3

All participants are underogoing the following within 3 months:

Clinical neurological and psychiatric examination.Comprehensive neuropsychological assessment.Structural and resting-state fMRI.24-h ambulatory (Holter) EEG.Blood sampling (all groups) and CSF sampling (MCI subset, where clinically indicated).

Data are stored in an anonymized research database (ACOL).

#### Neuropsychological assessment

2.3.1

Neuropsychological testing (Hungarian language versions) will be performed by trained neurologists or neuropsychologists using a unified UDS3-based battery (Boccardi et al., 2022). Instruments include:

Global cognition: Addenbrooke Cognitive Examination–Revised (ACE-R), Mini-Mental State Examination (MMSE).Memory and learning: Rey Auditory Verbal Learning Test (RAVLT: Sum of first five trials [Sum5], delayed recall after 30 min [Trial 7]).Attention and executive functions: Trail Making Test A (TMT-A: processing speed) and B (TMT-B: set-shifting).Visuospatial and constructional skills: Benson Figure Copy (immediate copy and delayed recall).Working memory: Number Span Backward (NSB).Language: Category (semantic) and phonemic verbal fluency.Mood and anxiety: Beck Depression Inventory-II (BDI-II), Spielberger State and Trait Anxiety Inventory (STAI-S, STAI-T).

Cut-offs for normal performance (e.g., MMSE > 25, age- and education-adjusted norms) will be applied for diagnostic purposes and covariate control. This battery has been validated and widely used by our group in previous cohorts (Berente et al., 2022; Csukly et al., 2016; Csukly et al., 2024; Unoka et al., 2026).

#### Structural MRI

2.3.2

All MRI examinations will be conducted on a 3T Siemens Magnetom Verio scanner using a 12-channel head coil. The protocol includes:

T1-weighted 3D MPRAGE (TR 2,300 ms; TE 3.4 ms; voxel 1 × 1 × 1 mm).Additional high-resolution T1-weighted 3D spoiled gradient echo (T1W 3D Turbo Field Echo; TR 9.7 ms; TE 4.6 ms; voxel 1 × 1 × 1 mm).T2-weighted, FLAIR, and 64-direction diffusion tensor imaging (DTI) sequences to evaluate lesions and white matter integrity.

Cortical reconstruction and volumetric segmentation will be performed using FreeSurfer 6.0 (“recon-all” pipeline with default parameters). Quality-checked outputs will provide cortical thickness and volume estimates in standard parcellations. DTI-based structural connectivity indices will be derived using established pipelines. The exact pipeline is described in previous studies published by our group (Bolla et al., 2025; Csukly et al., 2016).

#### Resting-state fMRI

2.3.3

Resting-state fMRI will be acquired using T2*-weighted echo-planar imaging (EPI) sequences (TR 2,000 ms; TE 30 ms; flip angle 70–79°; voxel 3 × 3 × 3–4 mm; ∼10-min duration). Participants will be instructed to remain still, keep their eyes closed (or fixate on a cross, as per the scanner-specific protocol), and avoid falling asleep.

Preprocessing and functional connectivity analysis will be performed with the CONN toolbox (MATLAB) using a standard pipeline:

Realignment and unwarping; slice-timing correction.Outlier detection (ART-based scrubbing).Direct segmentation and normalization (GM/WM/CSF, MNI space).Spatial smoothing.Band-pass filtering (0.008–0.09 Hz).Regression of white matter, CSF, and motion parameters.

Regions of interest (ROIs) will be defined *a priori* within the DMN, SN, and AN based on the literature and group consensus. Seed-based connectivity (SBC) analyses will compute Fisher-z-transformed correlations between ROI time series and voxel-wise signals. Age and sex will be included as covariates. Group differences (e.g., HC > MCI, HC > ASD, HC > ADHD) will be evaluated using voxel-wise ANCOVA with cluster-level FDR correction (cluster pFDR < 0.05; voxel *p* < 0.001 uncorrected). Hyperactivity will be defined as significantly elevated connectivity or activity within predefined network ROIs of DMN, SN, and AN relative to HC normative values obtained from our reference database (ACOL). For further details, see section “2.4.1 Participant selection and extraction of normative values.” Participants will be categorized as fMRI-positive or fMRI-negative for cortical hyperexcitability. The exact fMRI pipeline is characterized in previous studies published by our group (Bolla et al., 2023, 2025).

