#### Participant selection and extraction of normative values

2.4.1

Across all groups (HC, MCI, ASD, ADHD), participants with clear evidence of cortical hyperexcitability—defined by at least one of: SEA on EEG above a predefined density threshold; or fMRI-defined hyperactivity in DMN/SN/AN—are invited to participate. We will initially prioritize HC and MCI subjects during the pilot phase to refine the in-ward protocol, then extend to ASD/ADHD.

Normative values for the fMRI and EEG metrics will be calculated using the ACOL dataset. The ACOL dataset is our clinical registry, founded in 2014, and contains longitudinal data from 500 individuals at various stages of the cognitive continuum. The dataset includes 280 healthy individuals (mean age = 55) with records on clinical anamnesis, demographics, blood-based biomarkers, neurological examination, medications, neuropsychology, 24-h Holter-EEG, 10-min resting EEG, sMRI, 10-min resting fMRI, pupillometric data, fine-movement analysis, and autonomic functions. All participants have been scanned with the same MRI scanner (Siemens Magnetom 3T) and examined with the same EEG recording system (Micromed Morpheus Holter-EEG). Further details on the dataset can be found at the EuroFingers Consortium website^1^.

To generate normative fMRI values, we perform rigorous preprocessing of all scans—motion correction, spatial normalization, smoothing, and signal denoising—to ensure comparability across individuals. Next, functional metrics, including functional connectivity strength, regional homogeneity (ReHo), amplitude of low-frequency fluctuations (ALFF), Hurst-exponent, and network efficiency, are extracted for each subject. Within the healthy control group, these measures are then aggregated and standardized by computing the mean and standard deviation of each metric across all participants to generate z-score distributions that define the “normal” range. Statistical modeling (Gaussian mixture) is used to identify normative intervals and detect outliers. To account for biological variability, the dataset is stratified by relevant covariates such as age, sex, and head motion. The resulting normative models can then serve as a statistical reference framework, allowing patient metrics to be expressed as deviation scores (z-scores) that quantify brain abnormalities relative to typical controls.

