#### Cross-sectional analyses

2.6.1

Data from all diagnostic groups will be pooled into a single multivariate dataset and analyzed using machine learning and dimensional reduction techniques to extract cross-diagnostic patterns of neural and behavioral variance. The model will test for latent factors reflecting shared E/I imbalance across disorders, while *post hoc* analyses identify disorder-specific deviations. Statistical adjustments will account for confounders such as age, medication, and cognitive status.

Primary outcome will be the (Torenvliet et al., 2023) incidence and distribution of SEA, and fMRI hyperactivity in each diagnostic group relative to controls. Secondary outcomes will include relationships between hyperexcitability and (a) structural atrophy and white matter integrity; (b) functional connectivity within and between default mode, salience, and attention networks; (c) CSF and plasma tau/Aβ levels; and (d) domain-specific cognitive performance.

Incidence of hyperexcitability (primary outcome):○Logistic regression models comparing SEA and fMRI-positive status between groups (MCI, ASD, ADHD vs HC), adjusting for age, sex, education, and disease duration where applicable.○Results will be reported as odds ratios with 95% confidence intervals.

Associations with cognition, structure, and connectivity (secondary outcomes):○Within each group, participants will be classified as hyperexcitability-positive vs negative (see section “2.4.1 Participant selection and extraction of normative values”).○For continuous outcomes (neuropsychological scores, cortical thickness/volume, DTI measures, functional connectivity indices, blood-based biomarker concentrations), group comparisons will use *t*-tests or Mann–Whitney U tests depending on normality (Shapiro-Wilk).○For categorical variables, chi-square tests will be used.○Multivariable linear models with covariates (age, sex, education, disease duration, mood/anxiety scores) will assess independent associations.Holm–Bonferroni corrections will be used to control for multiple comparisons.

Cross-modal relationships:○Correlation and regression analyses will examine relationships between spike density and fMRI hyperactivity.○Multimodal latent variable models or clustering approaches will be applied exploratorily to define hyperexcitability phenotypes.

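### Head motion is a covariate for the fMRI norms but not for the patient-versus-control connectivity ANCOVA, nor for the secondary linear models of functional connectivity

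*Protocol article*

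**What the plan says.** **Within-scan motion handling (protocol article, 2.3.3 Resting-state fMRI).** The pipeline includes realignment and unwarping, "Outlier detection (ART-based scrubbing)" and "Regression of white matter, CSF, and motion parameters".

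**Group comparison (2.3.3).** For the seed-based connectivity analysis the article states "Age and sex will be included as covariates". Contrasts of controls with each patient group "will be evaluated using voxel-wise ANCOVA with cluster-level FDR correction (cluster pFDR < 0.05; voxel" p < 0.001 uncorrected).

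**Norms (2.4.1 Participant selection and extraction of normative values).** Before the norms are computed, "we perform rigorous preprocessing of all scans—motion correction, spatial normalization, smoothing, and signal denoising". Even so, "the dataset is stratified by relevant covariates such as age, sex, and head motion". Participants are labelled fMRI-positive or fMRI-negative against these norms.

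**Secondary models (2.6.1 Cross-sectional analyses).** The contrast is set by "Within each group, participants will be classified as hyperexcitability-positive vs negative". Functional connectivity indices are among the continuous outcomes. The adjusted analysis is "Multivariable linear models with covariates (age, sex, education, disease duration, mood/anxiety scores) will assess independent associations".

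**The concern.** Scrubbing and motion-parameter regression clean each person's time series. They do not adjust a comparison between people for whatever association between motion and connectivity is left. Section 2.4.1 accepts this: it corrects for motion and then still treats motion as relevant when setting the norms. The two group-level covariate lists do not.

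The exposure differs between the two places.

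- **ANCOVA in 2.3.3.** Adults with ADHD or ASD, older adults with MCI and controls may plausibly move by different amounts in a scan of about 10 minutes. If so, and if connectivity still depends on motion after preprocessing, part of a patient-control difference would be motion.
- **Linear models in 2.6.1.** Each comparison lies within one diagnosis. A motion term matters only if hyperexcitability-positive and negative participants move differently. The article does not say whether they do.

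The results at stake are the patient-control connectivity maps and, under that second condition, the Hypothesis 4 associations between hyperexcitability and connectivity.

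**Working it through.** **Covariate lists side by side**

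| Analysis | Motion handled within scan | Motion as between-person covariate |
|---|---|---|
| fMRI norms, 2.4.1 | yes | yes (with age, sex) |
| Control-versus-patient ANCOVA, 2.3.3 | yes | no (age, sex) |
| Linear models for connectivity, 2.6.1 | yes | no (age, sex, education, disease duration, mood/anxiety) |

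The article states no figure on this point, so there is none to reproduce.

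**Illustration of size**

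Inputs from the article (2.2.4): 75 per group, two-sided α = 0.05. Assumed inputs, because the article gives no motion data: motion gap g between groups in SD units, and residual motion-connectivity correlation r after preprocessing.

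With no true group difference, the spurious standardised difference is δ = g × r. For one ROI-level comparison:

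- SE = √(1/75 + 1/75) = 0.163
- rejection probability = Φ(δ/SE − 1.96) + Φ(−δ/SE − 1.96)

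Worked case, g = 0.5 and r = 0.3: δ = 0.15, δ/SE = 0.919, and the probability is Φ(−1.041) + Φ(−2.879) = 0.149 + 0.002 = 0.151.

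| g | r | δ | False-positive rate |
|---|---|---|---|
| 0.3 | 0.1 | 0.03 | 5.4% |
| 0.5 | 0.1 | 0.05 | 6.1% |
| 0.5 | 0.2 | 0.10 | 9.4% |
| 0.5 | 0.3 | 0.15 | 15.1% |
| 0.8 | 0.2 | 0.16 | 16.5% |
| 0.8 | 0.3 | 0.24 | 31.2% |

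If r = 0 or g = 0, the rate stays at 5%.

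**Check by simulation.** ANCOVA at 75 vs 75, 4,000 runs per case, no true group effect:

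| g | r | Age and sex only | Age, sex and motion |
|---|---|---|---|
| 0.5 | 0.2 | 9.3% | 5.2% |
| 0.5 | 0.3 | 14.9% | 4.8% |
| 0.8 | 0.3 | 30.7% | 4.8% |

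**Within-diagnosis comparisons (2.6.1).** At the roughly 15% prevalence assumed in 2.2.4, 0.15 × 75 ≈ 11, so the split is about 11 vs 64. SE = √(1/11 + 1/64) = 0.326, twice the value above. If g is read as a motion gap between positive and negative participants, biases of 0.10, 0.15 and 0.24 SD give 6.1%, 7.4% and 11.2% with a two-sample t-test, before the Holm–Bonferroni correction.

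**Limit of the illustration.** It is one ROI test at 5%. The planned voxel-wise p < 0.001 procedure with cluster-level FDR was not modelled.

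**The case against.** 1. **Motion is already handled.** Realignment, scrubbing and motion-parameter regression are standard, and section 2.5 adds visual checks and harmonised procedures. This stands to the extent that only residual motion is at issue. It does not remove the point, because 2.4.1 applies motion correction and still keeps motion as a covariate.
2. **Norms and group tests are different tasks.** Stratifying a reference database so that one person's score can be read is not the same as comparing group means. That is true, and the passages do not formally contradict each other. But if motion moves individual scores after correction, it can also move group means whenever groups differ in motion.
3. **This is a condensed article that cites earlier pipeline papers.** Further motion handling may be described there. But the covariates of the ANCOVA and of the linear models are stated outright, so this is a stated model choice and not an omitted detail.
4. **The affected ANCOVA is not itself a listed outcome.** This stands. The primary outcome is modelled on EEG-positive and fMRI-positive status, and Hypothesis 4 relates hyperexcitability, not diagnosis, to connectivity.
5. **Adjustment can overcorrect.** If motion is part of the disorder, a motion covariate may remove some true difference. This stands, and is the reason to keep the result without motion.

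A reader might infer that a patient-control motion gap biases the Hypothesis 4 results. It does not do so directly, because those contrasts are made within each diagnosis. A reader might also infer that the primary fMRI outcome is confounded by motion. The label comes from motion-stratified norms, so it is largely shielded.

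**Conclusion.** The point holds in a limited form. The control-versus-patient ANCOVA omits a covariate that the plan itself treats as relevant after motion correction, so a residual motion difference between patients and controls can bias that contrast. The 2.6.1 linear models for connectivity share the omission, but are exposed only if motion differs by hyperexcitability status within a diagnosis.

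The size is unknown. The 5% to 31% range rests on an assumed motion gap, an assumed residual correlation and a single ROI test at 75 vs 75. It should not be read as the error rate of the planned analysis. For splits near 11 vs 64 the same biases inflate the error much less. Cluster-level FDR and Holm–Bonferroni correction control chance findings; they do not remove a bias in the contrast. The change is worth making because it is cheap and brings the analyses into line with the plan's own covariate list, not because a large bias has been shown.

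**What to change.** - In 2.3.3, set the ANCOVA covariates to age, sex and each participant's mean head motion (or number of scrubbed volumes).
- In 2.6.1, add the same term to the linear models whose outcome is functional connectivity.
- Report the motion summary by diagnostic group and by hyperexcitability status, so readers can see whether confounding was possible.
- Keep the models without motion as a sensitivity analysis, and interpret any disagreement with overcorrection in mind.

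The motion summary comes from the existing realignment and ART output, so no new data or participants are needed. The cost is one degree of freedom per model and the possible loss of a little true difference where motion belongs to the disorder.

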**Association with functional connectivity.**
*Hypothesis 4:* Hyperexcitability is associated with altered resting-state functional connectivity within and between DMN, SN, and AN, indicative of maladaptive network reorganization.

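### Hyperexcitability status is partly defined by elevated DMN/SN/AN connectivity and then compared on connectivity from the same scan, which inflates the false-positive rate for Hypothesis 4

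*Protocol article*

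**What the plan says.** Four statements in the protocol article have to be read together.

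- **Label, fMRI part (section 2.3.3).** "Hyperactivity will be defined as significantly elevated connectivity or activity within predefined network ROIs of DMN, SN, and AN relative to HC normative values". Section 2.4.1 builds the normative values from "functional metrics, including functional connectivity strength, regional homogeneity (ReHo), amplitude of low-frequency fluctuations (ALFF") and further metrics, so connectivity strength is one of the quantities that can make a participant positive.
- **Label, composite rule (section 2.4.1).** A participant counts as hyperexcitable on at least one of two criteria: "SEA on EEG above a predefined density threshold; or fMRI-defined hyperactivity in DMN/SN/AN".
- **Comparison (section 2.6.1).** Within each diagnostic group, "participants will be classified as hyperexcitability-positive vs negative (see section" 2.4.1). The two classes are compared by t-test or Mann-Whitney U test, and in multivariable linear models, on a list that includes functional connectivity: "For continuous outcomes (neuropsychological scores, cortical thickness/volume, DTI measures, functional connectivity indices, blood-based biomarker concentrations").
- **Target (sections 2.6.1 and 1.2).** Secondary outcome (b) is the relation of hyperexcitability to "functional connectivity within and between default mode, salience, and attention networks". Hypothesis 4 reads: "Hyperexcitability is associated with altered resting-state functional connectivity within and between DMN, SN, and AN".

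The article describes one resting-state scan per participant (sections 2.3 and 2.3.3). It does not restrict the connectivity comparison to EEG-defined status, and it does not remove the label-defining metrics from the outcomes.

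**The concern.** Participants who enter the positive class through the fMRI criterion can do so because their connectivity in these networks is high. Comparing connectivity between the classes then partly recovers the selection rule. The difference appears even if epileptiform activity has no relation to connectivity.

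The planned safeguards do not address this. Holm-Bonferroni controls multiplicity, not selection on the outcome. Age, sex, education, disease duration and mood scores do not break the dependence. The external reference database sets the cut-off independently, but each participant's own connectivity value still decides the label.

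At stake is the meaning of a positive result. Section 3.2 would read an association between hyperexcitability and altered connectivity as evidence of network-level vulnerability, and under the planned comparison that reading would not be safe.

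**Working it through.** **The plan's own figure.** No power or error rate is stated for Hypothesis 4. The claim of more than 90% power in section 2.2.4 concerns the primary outcomes and is not used here.

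**Inputs from the article.** 75 per group, two-sided alpha 0.05 and d = 0.5 (section 2.2.4); the composite rule (section 2.4.1); t-test or Mann-Whitney U (section 2.6.1).

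**Assumed inputs.** The article gives no fMRI cut-off, number of metrics or correlation. The check used z > 1.645 or z > 1.96; 1, 3 or 9 standard-normal connectivity metrics (correlation 0.3 where there are several); and an SEA rate s of 5%, 15% or 30%. The 15% is the article's assumed prevalence of hyperexcitability overall, borrowed here for SEA. SEA is generated independently of connectivity, so Hypothesis 4 is false in every run.

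**Step 1: built-in difference, one metric.** Let a = P(Z > c), let φ be the normal density, and let p = s + (1 − s)a be the share positive. SEA-only positives have mean connectivity equal to the population mean, so

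Δ = (1 − s)φ(c) / [p(1 − p)].

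- s = 0.15, c = 1.645: p = 0.15 + 0.85 × 0.05 = 0.1925; Δ = 0.85 × 0.1031 / (0.1925 × 0.8075) = 0.56 SD (simulated 0.56).
- s = 0.30, c = 1.96: p = 0.30 + 0.70 × 0.025 = 0.3175; Δ = 0.70 × 0.0584 / (0.3175 × 0.6825) = 0.19 SD (simulated 0.20).

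With an EEG-only label Δ = 0.

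**Step 2: false-positive rate.** Simulated rejection for a single defining metric, composite label, equal-variance t-test at 0.05, 2,000 runs per cell (cut-off 1.645 / 1.96). Runs with fewer than three people in either class were dropped.

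| Metrics in label | SEA 5% | SEA 15% | SEA 30% |
|---|---|---|---|
| 1 | 76% / 49% | 49% / 25% | 29% / 14% |
| 3 | 79% / 55% | 61% / 34% | 37% / 19% |
| 9 | 86% / 68% | 73% / 52% | 54% / 33% |

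The range depends somewhat on the test. The equal-variance t-test gives 14% to 86%. With the Mann-Whitney and unequal-variance t-tests the range is about 9% (Mann-Whitney; one metric, SEA 30%, cut-off 1.96) to 84% (unequal-variance t-test; nine metrics, SEA 5%, cut-off 1.645). The more conservative range of 9% to 84% is carried forward.

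**Step 3: multiplicity.** At 15% SEA, at least one metric passes the first Holm step in 44-75% of runs with 3 metrics and in 74-93% with 9.

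**Step 4: between-network indices.** An index correlated 0.3 with the mean of the defining metrics is rejected in 6-31% of runs.

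**Step 5: EEG-only label on the same null data.** Rejection is 4.4-5.6% for within-network and 4.8-5.0% for between-network connectivity.

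**Step 6: power after the change.** If SEA is 15%, 0.15 × 75 = 11.25, so about 11 versus 64. The noncentrality is 0.5 / √(1/11 + 1/64) = 1.53 on 73 degrees of freedom, giving about 33% power. With 8 versus 67 it is about 26%.

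**The case against.** The strongest reply is that the overlap is only partial, and several parts of it stand.

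- **The test can fail.** A reader might infer that Hypothesis 4 is confirmed by construction. The documents do not support that. A difference is built in, but significance depends on the cut-off, the number of metrics and the share of positives who are SEA-only, and under some assumptions it is uncommon.
- **The label is wider than connectivity.** The rule covers connectivity or activity, and section 2.4.1 also lists ReHo, ALFF, the Hurst exponent and network efficiency. Participants positive on SEA or on an activity metric alone dilute the effect. How the metrics combine is not stated.
- **Hypothesis 4 also covers between-network connectivity**, whereas the label is defined within network ROIs. Those indices are affected only through their correlation with the defining metrics.
- **The most extreme figures belong to another label.** An fMRI-only label (three networks correlated 0.5, cut-off 1.645) gives about 92% rejection, against about 67% for the composite with 10% SEA. Section 2.6.1 refers to the composite for these analyses, so the 92% does not describe the planned test.
- **An EEG-only analysis already exists.** Section 2.6.1 relates spike density to fMRI hyperactivity. That serves Hypothesis 5. It is free of the circularity, but it does not replace the planned test of outcome (b).

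None of this removes the defect. The label and the comparison are both stated and are linked by explicit cross-reference, so this is not a detail left to an analysis plan.

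**Conclusion.** The concern holds as an inflated false-positive rate, not as a guaranteed result. In the planned comparison the same scan helps define the exposure and supplies the outcome, so a difference is built into secondary outcome (b) and Hypothesis 4. Under the assumed values a single defining within-network metric is significant in about 9% to 84% of null simulations, against about 5% with EEG-defined exposure. The width of that range reflects inputs the article does not give. The direction does not depend on them.

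Two wider readings are not supported. The primary outcome compares SEA and fMRI-positive status between diagnostic groups and is untouched. Cognition, structural MRI, DTI and fluid biomarkers do not define the label, so those comparisons are not circular. Section 3.3.1 describes feature discrimination as an implication for future research and not as a specified analysis, so the bias would reach a biomarker panel only if label-defining features were later assessed against that label.

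**What to change.** In section 2.6.1, state that for secondary outcome (b) and Hypothesis 4 the exposure is EEG-defined only: SEA status, and preferably continuous spike density, which limits the loss of power. State also that neither the composite nor the fMRI-positive label serves as exposure for any resting-state fMRI outcome, or that such a comparison is reported as descriptive only, without a p-value. If features that separate positive from negative cases are later assessed (section 3.3.1), exclude those that define the label.

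An alternative is to drop connectivity from the fMRI label for this analysis and keep the activity metrics. It is weaker, because ALFF and ReHo come from the same scan and some dependence would remain.

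The change is to wording and needs no new data, but it has a real cost. fMRI-only positives no longer count as exposed, and a binary EEG contrast at 15% SEA has only about one chance in three of detecting d = 0.5 within a group. The revised test also moves closer to the Hypothesis 5 analysis, so the text should say how the two differ.
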